## Abstract

**Background:**

Depressive disorders occur in 2 to 5% of the adolescents and are associated with a high burden of disease, a high risk of recurrence and a heightened risk for development of other problems, like suicide attempts. The effectiveness of cognitive behaviour therapy (CBT), cost-effectiveness of this treatment and the costs of illness of clinical depression in adolescents are still unclear. Although several Randomized Controlled Trials (RCT) have been conducted to establish the efficacy of CBT, the effectiveness has not been established yet. Aim of this study is to conduct a RCT to test the effectiveness of CBT and to establish the cost-effectiveness of CBT under rigorous conditions within routine care provided by professionals already working in mental health institutions.

**Method/Design:**

CBT is investigated with a multi-site, RCT using block randomisation. The targeted population is 140 clinically referred depressed adolescents aged 12 to 21 years old. Adolescents are randomly assigned to the experimental (*N* = 70, CBT) or control condition (*N* = 70, TAU). Four assessments (pre, post, follow up at 6 and 12 months) and two mediator assessments during treatment are conducted. Primary outcome measure is depression diagnosis based on a semi-structured interview namely the K-SADS-PL. Secondary outcome measures include depressive symptoms, severity and improvement of the depression, global functioning, quality of life, suicide risk, comorbidity, alcohol and drug use, parental depression and psychopathology, parenting and conflicts. Costs and treatment characteristics will also be assessed. Furthermore, moderator and mediator analyses will be conducted.

**Discussion:**

This trial will be the first to compare CBT with TAU under rigorous conditions within routine care and with a complex sample. Furthermore, cost-effectiveness of treatment and cost-of-illness of clinical depression are established which will provide new insights on depression as a disorder and its treatment.

## Background

Depressive disorders in adolescents are among the most prevalent disorders with a high burden of disease [1] and high risk of recurrence [2,3]. Before entering adulthood, 14 to 25% of the adolescents have experienced at least one episode of a depressive disorder [2]. Besides the high prevalence [4-7], comorbid psychiatric diagnoses are often present [8-10]. In addition, a heightened risk exists for development of social problems, juridical problems, learning problems, substance abuse, negative life events, physical problems, teen pregnancies and suicide [2,9,11]. Therefore, it is important that depression is treated in an early stage with an effective treatment [2,12].

In the international literature, there is no consensus on the degree of effectiveness of psychotherapeutic interventions in depressed adolescents. In a meta-analysis, which included studies with a large diversity of investigated interventions, only a modest effect size of 0.34 was found [13]. Other meta-analyses calculated medium (0.72) [14] to large (1.27) effect sizes [15]. In a meta-analysis solely directed at Cognitive Behavioral Therapy (CBT) a medium effect size of 0.53 was found [16]. Although the effect size for CBT is promising, it also reflects the need for improved treatment of depression, as a large group of depressed adolescents will not recover after CBT treatment.

In addition, it is often discussed that effectiveness studies in depressed adolescents lack generalizability for clinical practice, because the study samples do not match the complex and severe cases in routine mental health care [13]. In this study, this issue is addressed by comparing CBT to treatment as usual within a referred clinically depressed group of adolescents.

Within this study an individual revision of the group CBT program “Coping with Depression course for Adolescents” (CWD-A) [17] will be investigated. Group CBT was adapted into an individual CBT format because it is much better applicable within mental health care than group CBT, for instance children can start treatment immediately. Several RCT’s were conducted with an American population, but not with clinically referred adolescents. Results repeatedly have shown that the CWD-A was more effective than control conditions [18,19] and treatment as usual [20,21]. As only one research group investigated the CWD-A, it is regarded as probably efficacious [22].

The costs of depression in adolescents have not been studied before. Knowledge about costs of depression is essential to motivate an increase in budgets for treatments. A recent cost-of-illness study on children with anxiety disorders shows that both the costs of school absence, as well as productivity loss of the parents are substantial [23]. Given the high degree of comorbidity of anxiety and depression and the fact that both disorders are internalising disorders, the same high costs are expected in adolescents with depression. Lynch and colleagues [24] investigated cost-effectiveness of a group based prevention course “Coping with Stress” in adolescents with a subclinical depression. It was concluded that group CBT was more cost effective in comparison to treatment as usual. However, intervention related costs like productivity costs, expressed as school absence, were not taken into account. Including these costs could indicate that cost-effectiveness is even higher.

Within intervention research in depressed adolescents, little is known about possible moderators and mediators of treatment. A lot of authors mention the necessity to investigate factors that may be involved as such [13,22].

In conclusion, the efficacy of CBT for the treatment of clinically depressed adolescents is established, but the effectiveness is not yet clear. Cost effectiveness of CBT in comparison to Treatment As Usual (TAU) and potentially important moderators and mediators have not been investigated yet. Effectiveness, cost effectiveness, and information on moderators and mediators are essential for the enhancement of the treatment for depression in adolescence in order to reduce the burden of adolescent depression and recurrence.

## Methods and design

### 

#### Aim of the study

The aim of this study is to investigate the effectiveness and the cost-effectiveness of the individual CBT program the “D(o)epression course” in a sample of referred adolescents with a Depressive Disorder according to DSM-IV-TR [25] in a randomized controlled trial. We expect that CBT will be more effective than TAU (without CBT). Furthermore, cost-effectiveness of CBT and the cost of illness of clinical depression in adolescents will be established. Potential moderators (comorbidity, severity of depression, age, ethnicity, gender, suicidal thoughts and psychopathology in parents) and mediators (negative automatic thoughts, cognitive emotion regulation and attribution style) for the effectiveness of CBT will be studied. The role of non-specific treatment variables (therapeutic alliance, client expectancy, client satisfaction, treatment adherence) will be taken into account as well (see Figure 1).

**Figure 1 F1:**
[figure not shown]
Aims, conditions, potential moderators and mediators evaluated in this study.

#### Design

This study is designed as a multi-site, randomized controlled clinical trial in which individual CBT will be compared to TAU. Four multiple informant (adolescent, parent, therapist) assessments are done: prior to treatment (pre-test assessment), immediately after treatment (post-test assessment or after 15 sessions), 6 months after treatment (6 month follow-up) and 1 year after treatment (1 year follow-up). To investigate potential mediators two temporary assessments are conducted, each after 5 therapy sessions.

All sessions will take place within routine outpatient care within second order public mental health clinics to enhance external validity. All treatments in both conditions are delivered by psychologists with at least a master's degree-level and two years of experience within professional mental health care. These professionals are trained before delivering the treatments to enhance treatment integrity.

Adolescents who are diagnosed with a depression according to the K-SADS-PL [26,27], who meet inclusion criteria and do not meet the exclusion criteria are randomly assigned to either individual CBT or TAU. Random assignment per adolescent is executed using computer generated block randomisation and stratified per mental health centre. See Figure 2 for patient’s flow chart.

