#### Recruitment

The participants are recruited from fourteen different specialized mental health care institutions spread all over the Netherlands. An experienced psychologist within the mental health centre informs the adolescents and their parents about the study. After written informed consent by the adolescent and his/her parents, a trained independent researcher carries out an interview to check for the inclusion and exclusion criteria.

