#### Intervention

The experimental treatment is a protocolled individual CBT program, the D(o)epressie course. It consists of 15 weekly sessions of 45 minutes, two parent sessions after 3 and 9 weeks and a meeting with the parent at the end of treatment. The D(o)epressie course is, as the CWD-A, based on the social learning theory about the aetiology of depressions by Lewinsohn [28]. According to this theory, there is a connection between the number of positive interactions between a person and his environment on one hand, and depression on the other. A triggering event such as a stressful life event causes a negative spiral of less positive interactions leading to more negative thoughts and a deteriorating depressed mood. The aim of the intervention is to reduce depressive complaints in adolescents with a depressive disorder. Since depressive episodes are multi-factorial determined, the focus of the intervention is broad. The intervention contains representative components of CBT [29] namely: psycho-education (information about depression and the rationale for the aetiology of the complaints and the treatment of them), setting attainable goals (translate large goals into realistic short term goals), self monitoring (registration of the mood, activities and thoughts), activation (planning frequent, joyful activities), improving social skills and communication skills (improvement and stimulation of social behaviour), relaxation techniques, cognitive restructuring (identifying and changing unrealistic negative thoughts about the self, others and events), role play and problem solution skills (teaching the creation of solutions for problems via brainstorm, choosing, trying and evaluating) and relapse prevention. Exercises are executed within the sessions and are generalised into daily life by means of homework assignments. In the parent sessions, parents will receive psycho education and information on CBT. Therapists are not allowed to conduct treatments in both conditions.

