#### Instruments

In Table 1, concepts, source and time of assessment of all used instruments are presented. The adolescent and parent complete the self-report questionnaires online at home. Both, the adolescent and the parent have a separate login code to secure privacy. The parents fill in a paper version of the cost diary at home. The therapist completes the questionnaires at the office.

**Table 1 T1:** Instruments at different assessments and informants

	** *Domain/concept* **	** *Instrument* **	** *Items* **	** *Source* **			** *Test* **				
				** *A.* **	** *P.* **	** *T.* **	** *Pre* **	** *Med* **	** *Post* **	** *Fu1* **	** *Fu2* **
Primary outcome	Depression diagnosis	K-SADS		x	x		x		x	x	x
Secondary outcomes	Depression symptoms	CDI-II	28/17	x	x		x	x	x	x	x
	Depression severity	KSADS		x	x		x		x	x	x
		CGI-S	1			x	x	x	x		
	Depression Improvement	CGI-I	1			x	x	x	x		
	Global functioning	CGAS	1			x	x	x	x		
	Quality of life	EuroQol	6	x	x		x	x	x	x	x
	School or work	SQ	7	x			x		x	x	x
	Suicide Risk Taxation	SRT	6	x			x		x	x	x
	Comorbidity	K-SADS		x	x		x		x	x	x
		YSR	69	x			x		x	x	x
		CBCL	74		x		x		x	x	x
		SCARED	5	x	x		x		x	x	x
	Alcohol and drug use	AD	7	x			x		x	x	x
	Personality	Big 5	30	x			x		x		
	Life events	LES	23	x	x		x		x	x	x
	Parental depression	BDI-II	21		x		x		x	x	x
	Parental Psychopathology	ASR	69		x		x		x	x	x
		SCARED	4		x		x		x	x	x
	Parenting			x	x		x		x		
	-Responsivity	NOV	8								
	-Consistency	PDI	8								
	-Positive parenting	APQ	6								
	-Harsh discipline	SOG	8								
	-Psychological control	PCS	8								
	-Behavioural control	VTH	6								
	Competence	NOSI	5		x		x		x		
	Attachment	PARA	13	x	x		x		x		
	Conflict	NRI	6	x	x		x		x	x	x
Cost-effectiveness	Costs	Cost questionnaire			x		x		x	x	x
	Quality of life	EuroQol		x	x		x	x	x	x	x
Moderators	Demographic	Gender	8/12	x	x		x		x	x	x
	Characteristics adolescent	Age									
		Ethnicity									
		Education									
		Income									
	Depression severity	K-SADS		x	x		x		x	x	x
	Comorbidity	YSR			x		x		x	x	x
		CBCL		x			x		x	x	x
	Parental depression	BDI			x		x		x	x	x
	Parental Psychopathology	ASR			x		x		x	x	x
Mediators	Negative automatic thoughts	CNCEQ	16	x			x	x	x	x	x
	Cognitive Emotion regulation	CERQ	36	x			x	x	x	x	x
	Attribution style	CASQ	24	x			x	x	x	x	x
Treatment characteristics	Expectancy of treatment	PETS	7	x	x		x				
	Previous treatment	VEHI	8	x	x		x		x	x	x
	Satisfaction with treatment	SSS	4	x	x				x		
	Cooperation with treatment	CWT	5			x		x	x		

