Several non-specific treatment variables will be investigated. The client’s credibility, expectancy and involvement regarding treatment are assessed with the Parent Expectancies for Therapy Scale (PETS) [64] which was revised for adolescents. Previous treatments for depression, including complementary and self-help treatments, are administered with the inventory of History of Treatments (VEHI) [65]. Satisfaction with treatment is measured with the Service Satisfaction Scale (SSS) [66]. The Cooperation With Treatment scale (CWT) [67] is used to assess the degree of cooperation with treatment as observed by the therapist. The quality of the therapeutic alliance is assessed with the Therapy Alliance Scale for Adolescents (TASC) [68]. The content of treatment is assessed in both conditions with the Therapy Procedure Checklist (TPC) [69]. Treatment integrity will be established by recording two randomly chosen sessions that are observed and rated.

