### Statistical analyses

Missing values will be imputed. Intent-to-treat as well as completer analyses will be conducted. The effect of the intervention is analyzed with a chi-square test on the dichotomous primary outcome measure, presence of the depression diagnosis (K-SADS-PL). The cost-effectiveness analyses will be based on the comparison of costs and effects in both conditions and will be done according the international guidelines [70]. The cost- effectiveness analyses will be done separately from the perspective of mental health and society over a period of 6 months and 1 year. The effects of societal costs will be expressed in years to live, corrected for quality of life (QALYs). The costs of CBT versus CAU will be expressed in 1) incremental costs per QALY and 2) incremental costs per adolescent with a depression in full remission.

The secondary continuous outcome measures will be analyzed with repeated measures MANCOVA using the pre-test as a covariate as is recommended for RCT’s with pre-, post- and follow-up measurements [71]. For each questionnaire, the effect size (Cohen’s d) from pre- to post-treatment is defined as (M_pre_-M_post_)/SD_pooled_, where SD_pooled_ = [(SD_pre_^2^ + SD_post_^2^)/2]. CBT versus TAU pre-post effect sizes are calculated as follows [(M_CBT post_-M_TAU post_)/SD_pooled post_] – [ (M_CBT pre_-M_TAU pre_)/SD_pooled pre_]. Furthermore, analyzes will be conducted to establish clinical significance and the reliable change index [72].

Moderators will be analysed by multi-group analyses for dichotomous variables. The continuous variables will be analysed using hierarchic regression analyses. Mediator effects will be analysed using hierarchical regression analyses and structural equation modelling.

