First, content of TAU and the techniques used are difficult to monitor. Assessment of the therapeutic procedures used during each session by the therapist, provides detailed information on the components of the treatment. Also two sessions are recorded at random, observed and rated in detail to assess content of treatment and techniques used.

Second, comparing CBT to an active control condition may lead to a lower mean effect size than CBT versus a non-active control condition [13]. The TAU condition in this study is heterogeneous and it contains also evidence-based treatments such as Interpersonal therapy. As a result the ES can be even smaller, so we increased the power accordingly.

Third, to include 140 adolescents within 18 months, cooperation with a large group of mental health institutions is necessary. Furthermore, we try to minimize the effort the adolescent and their parents have to put into the study by using online assessments of the self-report questionnaires, while ensuring secrecy. Since the K-SADS-PL is assessed in vivo, not only self-report, but also observations by an independent clinician are taken into account.

Fourth, non-response may be a huge problem because of the multiple assessments and informants. Online assessment enables the researchers to monitor the progress per assessment per informant. They can react immediately to non-response and increase the response rate accordingly. This transparent logistic process of data collection, data transportation and data file construction reduces the risk of mistakes, missing data and contributes to the quality of the data [74].

Fifth, as it is not allowed to conduct CBT within the TAU condition it is inevitable that TAU is changed in this regard. This is a methodological problem, which may lead to bias, but cannot be solved properly. Although we are fully aware of this methodological problem we accept it because of the advantages of an RCT in a naturalistic setting. The preferred choice of treatment by the multidisciplinary team for every included depressed adolescent is registered and enables us to take into account the preferred choice of treatment.

Sixth, the total amount of face-to-face contact within TAU can be different from CBT. Also the time period in which the treatment is completed can differ within TAU and CBT. The amount of face-to-face contact in minutes and the time period of the treatment will be taken into account as potential moderating factors.

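### Therapist-rated pre-test scores (CGI-S, and CGAS as listed in Table 1) appear to be given after allocation by a therapist tied to one arm, yet they serve as the baseline for those two outcomes

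*Protocol article*

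**What the plan says.** **Timing.** The Design section names adolescent, parent and therapist as informants and sets the first assessments as "prior to treatment (pre-test assessment), immediately after treatment (post-test assessment or after 15 sessions". The same section says that adolescents with a K-SADS-PL diagnosis "who meet inclusion criteria and do not meet the exclusion criteria are randomly assigned to either individual CBT or TAU". Under Recruitment, "a trained independent researcher carries out an interview to check for the inclusion and exclusion criteria". Only the diagnostic and eligibility interview is thus placed expressly before randomisation.

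**Raters.** Table 1 ("Instruments at different assessments and informants") gives the therapist as the only source for CGI-S, CGI-I and CGAS, and marks all three at pre-test, mediator test and post-test, with no follow-up. The Secondary outcome measures section agrees for CGI-S, but for CGAS it names an independent clinician as well as the therapist. It gives K-SADS-PL severity to the independent clinician.

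**Therapists.** The Intervention section states: "Therapists are not allowed to conduct treatments in both conditions".

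**Use.** The Statistical analyses section plans, for the continuous secondary outcomes, a "repeated measures MANCOVA using the pre-test as a covariate". Its CBT-versus-TAU effect size subtracts the standardised pre-test difference between arms from the standardised post-test difference.

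**Preferred treatment.** The Discussion says: "The preferred choice of treatment by the multidisciplinary team for every included depressed adolescent is registered". Table 1 lists the same item with the therapist as source, at pre-test.

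**The concern.** A baseline covariate is safe in a randomised comparison because the allocation cannot have influenced it. A rating made once the arm is known lacks that protection. If the treating therapist follows from the allocation, the pre-test CGI-S and CGAS come from two separate groups of raters, one per arm, each aware of the treatment about to be given. A CBT therapist who rates the starting point as somewhat more severe would make the later improvement look larger, and both planned analyses would carry part or all of that shift into the estimated effect.

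The preference item matters for a different reason. The article admits that barring CBT from TAU may introduce bias that cannot be properly solved, and it offers the registered preference as a way to take this into account. If the allocated therapist records it with the arm known, it may no longer reflect the team's independent choice.

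**Working it through.** **Step 1: who is the therapist at pre-test?**

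- Table 1 uses one therapist column for all its rows. Besides CGI-S and CGAS, that column supplies the cooperation-with-treatment scale and the checklist completed at each session. Only the treating therapist can fill in those two.
- CGI-S and CGAS each occupy one row covering pre-test, mediator test and post-test, with no change of rater noted.
- Each therapist works in one condition, so the treating therapist cannot be known before allocation.
- The article mentions one other clinic-side person, the psychologist who informs families under Recruitment, but never calls that person the therapist. If that person did rate at pre-test, the rater would change before the mediator test without mention.

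The natural reading is a post-allocation rating with the arm known. This is a strong inference, not a stated fact.

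**Step 2: which baselines does this reach?** CGI-S, and CGAS as Table 1 lists it. CGI-I is defined relative to the start of treatment, so its pre-test mark cannot serve as a baseline at all. K-SADS-PL diagnosis, severity and comorbidity come from the interview before randomisation.

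**Step 3: the yardstick.** The Sample size section expects d = 0.53, with alpha 0.05 (taken as two-sided), power 0.80 and 20% drop-out. Then n per arm = 2 × (1.96 + 0.8416)² / 0.53² = 15.70 / 0.2809 = 55.9, rounded up to 56, and 56 / 0.80 = 70. The stated 70 per arm is reproduced. It does not change here; 0.53 is used only for scale.

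**Step 4: a shift at pre-test only.** Let s be the between-arm shift in SD units and r the pre-post correlation, with equal SDs at both times. The documents give neither value.

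- Covariate-adjusted effect = post difference − r × pre difference, so it moves by r × s.
- Effect-size formula = post difference − pre difference, so it moves by s.

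| s | r = 0.3 | r = 0.5 | r = 0.7 | effect-size formula |
|---|---|---|---|---|
| 0.1 | 0.03 | 0.05 | 0.07 | 0.1 |
| 0.2 | 0.06 | 0.10 | 0.14 | 0.2 |
| 0.3 | 0.09 | 0.15 | 0.21 | 0.3 |

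Against 0.53, the adjusted range is 0.03/0.53 = 6% to 0.21/0.53 = 40%. The effect-size range is 0.1/0.53 = 19% to 0.3/0.53 = 57%.

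**Step 5: a constant difference c between the two groups of raters, at pre-test and post-test alike.**

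- Effect-size formula: c − c = 0.
- Adjusted effect: c − r × c = (1 − r) × c. With c = 0.3 and r = 0.5 this is 0.15 SD.
- Independent-clinician pre-test paired with therapist post-test: nothing offsets c in the post-test rating under subtraction or adjustment, so the full 0.30 SD remains in both.

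**Step 6: preferred treatment.** The Discussion and Table 1 name different sources. If the therapist only passes on a team decision made earlier, the item is sound; if the therapist forms or records it after allocation, it may be coloured by the arm. The article does not say which.

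**The case against.** The strongest reply is that being prior to treatment is compatible with being before randomisation, that the participant flow chart is not shown, and that a condensed article need not spell out the order. Table 1 also puts the K-SADS-PL, which does precede randomisation, in the same pre-test column as everything else. And since Table 1 has no column for the independent clinician or the team, its therapist column might stand for clinic staff in general.

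Much of this stands. A reader might infer that the whole baseline is a post-randomisation, unblinded measurement and that every continuous secondary outcome is affected. The documents do not support that. The K-SADS-PL is done by an independent researcher before allocation. For the adolescent and parent questionnaires, the order relative to randomisation is simply unstated. The expectancy scale, by which "credibility, expectancy and involvement regarding treatment are assessed", is in the same position: its wording does not show that it refers to the assigned arm.

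The reply does not dispose of CGI-S and CGAS. There the point rests on two stated design choices, a therapist rating at pre-test and therapists confined to one arm. Reading the column as clinic staff in general fits poorly with the other items it covers. The two sources for preferred treatment, and the two accounts of who rates CGAS, need no inference.

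The objection is also right about size and remedy. The illustration depends on assumed inputs and on the shift being confined to pre-test. Simply replacing the therapist's baseline by an independent clinician's, while keeping the therapist's post-test, could make a constant rater difference worse (step 5).

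**Conclusion.** The point holds for two secondary scales and for the preference item. As written, the pre-test CGI-S, and CGAS as Table 1 lists it, are very probably arm-aware ratings made after allocation, and the planned covariate adjustment and effect size treat them as if they were ordinary baselines. A pre-test-only shift of 0.1 to 0.3 SD would move the adjusted effect by 0.03 to 0.21 SD and the effect-size formula by 0.1 to 0.3 SD. This assumes a pre-post correlation of 0.3 to 0.7, equal SDs, and that the pre-test rater is the treating therapist. A constant difference between the rater groups would behave differently.

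A reader might go on to doubt the main result. There is no ground for that: the primary analysis is a chi-square test on K-SADS-PL diagnosis and uses no pre-test covariate. Nor is the timing of the adolescent and parent questionnaires shown to be wrong.

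**What to change.** - **Design:** define the pre-test as completed before randomisation instead of before treatment.
- **Severity and functioning analyses:** base them on the independent clinician's K-SADS-PL severity and CGAS, with the same type of rater at pre-test and post-test. Add the independent clinician's CGAS, with its time points, to Table 1 so that it agrees with the Secondary outcome measures section.
- **Therapist CGI-S and CGAS:** report them as supportive, and do not treat the therapist's pre-test rating as a pre-randomisation baseline. Do not pair an independent baseline with a therapist post-test as the remedy.
- **Preferred treatment:** record the multidisciplinary team's choice before randomisation and correct the source in Table 1.

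**Cost:** allocation may be released slightly later, and the therapist-rated scales carry less weight. The article already assigns K-SADS-PL severity and a CGAS rating to the independent clinician, so no new instrument is needed. An independent CGI-S would be a new rating and is not required.

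### Post-test and both follow-ups are timed from the end of a treatment whose length can differ by arm, so the arms may be compared at different times since randomisation; the economic horizons have no stated origin

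*Protocol article*

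**What the plan says.** Protocol article, Design: the post-test and the two follow-ups take place "immediately after treatment (post-test assessment or after 15 sessions), 6 months after treatment (6 month follow-up) and 1 year after treatment (1 year follow-up". The two mediator assessments are timed by session count: "To investigate potential mediators two temporary assessments are conducted, each after 5 therapy sessions".

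Protocol article, Intervention: of the CBT programme, "It consists of 15 weekly sessions of 45 minutes". The same section lists a wide range of TAU, from medication and counselling to family therapy and running therapy. It gives neither a length nor a session frequency for any of them.

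Protocol article, Discussion (sixth anticipated problem): "Also the time period in which the treatment is completed can differ within TAU and CBT". The stated handling is that contact minutes and "the time period of the treatment will be taken into account as potential moderating factors".

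Protocol article, Statistical analyses: the effect is "analyzed with a chi-square test on the dichotomous primary outcome measure, presence of the depression diagnosis (K-SADS-PL", with no term for elapsed time. The cost-effectiveness analyses "will be done separately from the perspective of mental health and society over a period of 6 months and 1 year", with no starting point named. Table 1 collects costs at pre-test, post-test and the two follow-ups only.

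**The concern.** The visit clock starts at an event that comes after randomisation and that the assigned arm can influence. Depression remits and recurs over time. If one arm is assessed later than the other, its chance of being free of the diagnosis differs for that reason alone, and a chi-square test on the diagnosis cannot separate this from a treatment effect. The primary comparison is therefore open to a bias of unknown sign.

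The economic evaluation has a related problem. Its horizons are given as 6 months and 1 year, but the cost visits after baseline all inherit the end-of-treatment clock. The article does not say whether the periods start at randomisation, at the start of treatment or at its end. If they start at the end, the cost of the treatments being compared falls outside them.

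**Working it through.** **Inputs from the article.** CBT: 15 weekly sessions. Post-test at end of treatment or after 15 sessions; follow-ups 6 and 12 months after treatment. d = 0.53, alpha 0.05, power 0.80, drop-out 20%, 70 per arm.

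**Assumed, not in the article.** TAU length T (8 to 39 weeks, the same for every TAU patient); a constant remission rate, equal in both arms, with half-life H (26 weeks, varied from 16 to 39); no relapse.

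**1. The plan's own figure.** Two-sided comparison of means at d = 0.53: n = 2 × (1.96 + 0.84)² / 0.53² ≈ 56 per arm, and 56 / 0.8 = 70. The stated 70 per arm is reproduced and is not in dispute. The 56 completers per arm are used below.

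**2. Visit times.** Counting from the start of treatment, CBT given as planned is assessed at weeks 15, 15 + 26 = 41 and 15 + 52 = 67. TAU is assessed at T, T + 26 and T + 52. The difference is T − 15 weeks at every visit: −7, +5, +11 and +24 weeks for T = 8, 20, 26 and 39, and 0 for T = 15.

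**3. What that could do to the primary outcome.** Proportion still depressed at week t = 2^(−t/H). With H = 26 and no treatment effect, CBT at post-test is 2^(−15/26) = 67.0%. Gaps are CBT minus TAU in percentage points, from unrounded values; a positive gap favours TAU.

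| T (weeks) | TAU still depressed at post-test | Gap at post-test | Chance of p < 0.05 in that direction, 56 per arm | Gap at 6-month follow-up | Gap at 1-year follow-up |
|---|---|---|---|---|---|
| 8 | 80.8% | −13.8 | 38% | −6.9 | −3.4 |
| 15 | 67.0% | 0 | – | 0 | 0 |
| 20 | 58.7% | +8.4 | 15% | +4.2 | +2.1 |
| 26 | 50.0% | +17.0 | 45% | +8.5 | +4.3 |
| 39 | 35.4% | +31.7 | 93% | +15.8 | +7.9 |

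At T = 26, moving H between 16 and 39 weeks gives a post-test gap of 13.6 to 19.8 points. Over the whole grid (H = 16, 26, 39; T = 8, 20, 26, 39) the 1-year gap is 1.1 to 10.6 points in absolute size. The shrinkage over time follows from assuming no relapse.

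**4. Does the 15-session alternative close the gap?** If it acts as a cap and TAU is given in weekly sessions, TAU cannot run past about week 15 before post-test, and the rows with T above 15 drop out. At an assumed fortnightly frequency the cap is reached only at 15 × 2 = 30 weeks, and for TAU not organised in sessions it has no clear meaning. It does nothing for TAU that ends sooner. It also leaves open whether the follow-up clock of a patient still in treatment starts at session 15 or at the true end.

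**5. Does the moderator analysis close it?** Treatment length arises after randomisation and can depend on the arm. Patients with equal treatment length in the two arms are no longer comparable by randomisation, and the chi-square comparison itself is unchanged.

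**6. Economic horizons.** 15 weeks = 15 × 12 / 52 = 3.46 months. For CBT as planned, the follow-up cost visits fall 3.46 + 6 ≈ 9.5 and 3.46 + 12 ≈ 15.5 months after the start of treatment. For TAU with T = 26 they fall at weeks 52 and 78, against 41 and 67 in CBT. None of these visits is set at 6 or 12 months from randomisation.

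**The case against.** Much can be said on the other side.

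- Status at the end of treatment as delivered is a legitimate target in a routine-care trial, and a fixed-time visit changes the question. This stands as a real downside of the fix. It does not make assessments at different times comparable.
- The 15-session alternative is not restricted to CBT and may hold TAU close to the CBT clock. This stands in part: it limits delay if TAU is weekly, which the article does not say.
- The authors foresaw the problem and planned to examine treatment period as a moderator. They deserve credit for that, but the analysis does not repair the comparison.
- The economic origin may be defined in the full protocol. That is possible, but the text as published can be read in more than one way, and its own cost schedule does not match the periods it names from randomisation.

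A reader might go further in three ways that the documents do not support:

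- That the arms *will* be assessed at different times. The Discussion says only that the period can differ.
- That every assessment after baseline is tied to the end of treatment. The mediator assessments follow session counts, although these are not tied to randomisation either.
- That costs and QALYs will accumulate over unequal spans. With an assumed utility of 0.7 and TAU lasting 6 months, that would add 0.7 × (6 − 3.46) / 12 ≈ 0.15 QALY to TAU through observation time alone. This arises only if each arm's total runs to its own last visit. The article names one period for both arms and does not say how the visits map onto it.

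**Conclusion.** The point holds as a foreseeable risk, not as a demonstrated bias. Followed as written, the plan can compare the arms at different times since randomisation, and neither the 15-session alternative nor the moderator analysis rules this out. The sign and size cannot be determined from the article. The effect is nil if TAU also takes about 15 weeks. In the illustration it is largest at post-test (13.8 to 17.0 points for TAU of 8 or 26 weeks) and a few points at one year in those two cases. Those figures rest entirely on assumed TAU durations and a common remission rate without relapse. The article states no target difference in diagnosis rates, only d = 0.53, so they cannot be set against a planned effect on the same scale.

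On the economic side, the firm finding is that the 6-month and 1-year periods have no stated origin and that no cost visit is designed to fall 6 or 12 months after randomisation. Severity: should-fix.

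**What to change.** - Schedule the existing post-test and two follow-ups at the same times from randomisation in both arms: post-test at the planned end of the 15-week course, then 6 and 12 months later. Hold them whether treatment is continuing, finished or stopped early.
- Accumulate costs and QALYs from randomisation, including the treatment period, over the same fixed windows in both arms, and state those windows in place of the present wording.
- For patients already assessed, record time since randomisation and adjust for it in a sensitivity analysis. It can be no more than that, because elapsed time in those patients may itself depend on the arm.
- Treatment period can stay as a descriptive or exploratory variable, but not as the remedy for unequal timing.

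Cost: changes to visit scheduling and analysis wording, with no extra visits and the sample size still 70 per arm. Downside: some TAU patients will still be in treatment at post-test, so the result describes status at a fixed time and not at the end of treatment.
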